### Exclusion criteria

2.4

Participants meeting one or more of the following criteria will be excluded:

1.Experience with severe drug hypersensitivity to a particular drug or inability to take oral drugs;2.Currently pregnant or breastfeeding (fertile women will be required to use adequate contraception during the study period);3.Presence of metastatic cancer in the central nervous system or in need of concurrent therapy, such as primary site radiation therapy, chemotherapy, or immunotherapy;4.T790 M (threonine-to-methionine amino acid change at position 790) of the EGFR kinase domain (acquired, re-biopsy) mutation-positive;5.The presence of other serious disease:(a)Uncontrollable congestive heart failure or unstable angina, myocardial infarction within 1 year of study participation, uncontrollable hypertension or high-risk arrhythmia,(b)Inability to understand the research content due to neurological or psychiatric disorders, such as dementia and seizures,(c)Uncontrollable infections, such as tuberculosis and hepatitis;6.A history of diagnosis or treatment of malignant tumors other than NSCLC;7.Participation in research involving the combined administration of any other drug, except for afatinib, and in any other clinical trial within the previous 2 weeks;8.A need for administration of immuno-inhibitors or platinum-based chemotherapy after a PD-L1 expression test with multiple metastases with symptoms;9.Use of a prohibited medication during this clinical trial;10.Unsuitable for this clinical trial as determined by the researcher.

### Interventions

2.5

Patients in the treatment group 1 will receive afatinib (40 mg/day orally) plus HAD-B1 2 tablets (972 mg/day, bid orally) and placebo 2 tablets, those in the treatment group 2 will receive afatinib (40 mg/day orally) plus HAD-B1 4 tablets (1944 mg/day, bid orally), while those in the control group will receive afatinib (40 mg/day orally) plus placebo 4 tablets (bid orally). Afatinib, HAD-B1 and/or placebo will be administered consistently for 12 weeks; the trial may be terminated before the end of 12 weeks due to the development of unacceptable toxicities or withdrawal of the participant from the treatment.

The HAD-B1 tablets used in clinical trial will purchased from the Gyeongbang Pharmaceutical Co., Ltd. (In-cheon, Korean) and will meet the requirements of Good Manufacturing Practice (GMP). HAD-B1 is a medical substance that contains *Panax ginseng C.A.* (640 mg), *Panax notoginseng Radix* (839 mg), *Cordyceps militaris* (640 mg), and *Boswellia carterii BIRDWOOD* (480 mg) as raw material medicines is extracted for 16 hin purified water at 60°C. Then, the filtrate is concentrated under reduced pressure to obtain a dry extract of 486 mg. From this, 650 mg of one brown film-coated tablet is produced by adding excipients.^[10]^ The matching placebo will be purchased from the same manufacturer and consist of starch with no active ingredients.

### Outcome measures

2.6

The primary outcome is a comparison of the disease control rates (DCR) among treatment groups 1 and 2 and the control group after 12 weeks compared to baseline, which will be assessed from the date of randomization to 12 weeks, as determined by chest X-ray, CT or MRI according to the RECIST criteria.^[11]^

The secondary outcomes are comparisons of the complete response (CR) and the partial response (PR) to the treatment, the stability of the disease (SD), progression free survival (PFS), time to progression (TTP), and tumor marker (CEA, NSE) and WBC differential count (LMR, NLR) and natural killer cell activity and QOL (EORTC QLQ-C30) among treatment groups 1 and 2 and the control group after 6 weeks and 12 weeks compared to baseline.

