#### Analysis group

2.10.1

The data obtained from the subjects of this clinical trial will mostly be divided into a safety group, a FAS (full analysis) group and a PP (per protocol) group. The safety group will include participants who took the HAD-B1 or the placebo at least once. The FAS group will include participants who received the clinical trial medication, followed by one or more measurements of the primary outcome. Participants in FAS group who violate major inclusion, exclusion criteria or have never taken drug for clinical trial can be excluded. The PP group will include participants from among the FAS group who successfully completed this clinical trial according to the trial plan. Participants in PP group who violate test plan or take forbidden drug or do not obey a schedule can be excluded.

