### Principles of interpretation of results

2.11

The main analysis will be the FAS group analysis for the validity evaluation. The PP group analysis will be carried out separately to evaluate whether or not any differences from the FAS analysis results exist. For the FAS group, if a defect value happens at any point or a dropout occurs before the clinical trial ends, the most recent data will be analyzed as if it were obtained at that point in time (Last Observation Carried Forward Analysis). The SG analysis will be conducted to assess safety. All statistical analyses will be performed with SPSS version 21.0; no interim analyses will be performed.

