### Analysis of first outcome variables

2.13

Descriptive statistics (number in each group, average, standard deviation, minimum value and maximum value) will be used for each variable affecting the DCR (CR, PR, and SD), and the results for the two test groups and the control at the last visit versus the results at baseline will be presented. The statistical significance of any difference found between test groups and the placebo group will be analyzed using chi squared test. If any difference among three groups (2 test groups and 1 placebo group) is found, Bonferroni or Duncan method will be used. Chi squared test between placebo group and treatment group 1, placebo group and treatment group 2 will be additionally conducted.

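### The primary DCR can be read as week-12 status or as best status to week 12, and last visit with LOCF credits 12-week control to patients who die or leave early

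*Protocol article*

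**What the plan says.** All references are to the protocol article.

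- **Section 2.6, Outcome measures.** The primary outcome is a three-group comparison of DCR "after 12 weeks compared to baseline, which will be assessed from the date of randomization to 12 weeks", by imaging under RECIST. The secondary outcomes, which include CR, PR and SD, are compared "among treatment groups 1 and 2 and the control group after 6 weeks and 12 weeks compared to baseline".
- **Section 2.13, Analysis of first outcome variables.** DCR is described through its components, complete response, partial response and stable disease. On timing, the section says that "the results for the two test groups and the control at the last visit versus the results at baseline will be presented". Week 12 is not mentioned there.
- **Section 2.11, Principles of interpretation of results.** In the full analysis set (FAS), after a missing value or a dropout, "the most recent data will be analyzed as if it were obtained at that point in time".
- **Section 2.10.1, Analysis group.** "The FAS group will include participants who received the clinical trial medication, followed by one or more measurements of the primary outcome".
- **Section 2.5, Interventions.** Treatment is planned for 12 weeks and can stop sooner because of toxicity or because a patient withdraws.

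**The concern.** The primary sentence joins a status at a time point to an assessment over a period and does not say which one decides whether a patient counts as controlled. Because CR, PR and SD are also compared at week 6, there is an intermediate assessment on which the two can disagree. If the rule is left open, it can be chosen after the data are seen, and the choice moves the level of the primary result and probably the apparent difference between arms.

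A second weakness lies in the rule as written. A patient with SD or PR at week 6 who then dies or leaves has that scan carried to week 12 and is counted as controlled at 12 weeks. Nothing in sections 2.6, 2.11 or 2.13 makes death a failure.

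**Working it through.** **The plan's own figure.** Section 2.9 inflates 15 per group for 30% dropout: 15/(1 - 0.3) = 21.43, rounded up to 22, and 3 x 22 = 66. This reproduces. No DCR enters the calculation, so the timing question does not affect the sample size.

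**How each rule classifies the same patient**

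| Patient | Week-12 status | Best status to week 12 | Last visit with LOCF |
|---|---|---|---|
| SD at week 6, SD at week 12 | controlled | controlled | controlled |
| SD at week 6, progression at week 12 | failure | controlled | failure |
| SD at week 6, then dies or leaves | not observed | controlled | controlled |

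For completers, last visit and week 12 agree, and only best status differs. For patients who leave, last visit and LOCF give the same answer as each other.

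**Size, as an illustration.** The article states no DCR, so the following are assumptions:

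- Progression is exponential with median m = 9 to 12 months, the median PFS range in the Discussion.
- Scans fall at weeks 6 and 12. Section 2.6 suggests this through the secondary outcomes; the schedule table is not shown.
- For LOCF, the 30% dropout of section 2.9 falls wholly between the two scans and is independent of progression.

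Formula: S(t) = exp(-ln 2 x t/m), with m in weeks. Nine months is 9 x 365.25/12/7 = 39.13 weeks; twelve months is 52.18 weeks.

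| Quantity | m = 9 months | m = 12 months |
|---|---|---|
| Best status = S(6) | 0.899 | 0.923 |
| Week-12 status, all followed = S(12) | 0.809 | 0.853 |
| Gap (unrounded inputs) | 0.091 | 0.071 |
| Patients per arm, 22 x gap | 1.99 | 1.56 |
| Last visit/LOCF = 0.7 x S(12) + 0.3 x S(6) | 0.836 | 0.874 |
| Missing scan counted as failure = 0.7 x S(12) | 0.566 | 0.597 |

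Over three arms the gap between best status and week-12 status is 66 x 0.071 to 66 x 0.091, about 4.7 to 6.0 patients. With the upper figure of 13 months from the Introduction, S(6) = 0.929 and S(12) = 0.863, and the shift falls to about 1.45 per arm.

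The LOCF excess over S(12) is 0.3 x the gap: 0.021 to 0.027, or about half a patient per arm. It depends on independent dropout. If every patient who progressed between the scans left before the second one, LOCF would return S(6), that is 0.90-0.92.

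**Effect on the contrast between arms.** With an assumed hazard ratio of 0.5, survival in the treated arm is S(t)^0.5. At week 12 the differences are 0.899 - 0.809, about 0.09, and 0.923 - 0.853, about 0.07. On best status they are 0.948 - 0.899 = 0.049 and 0.961 - 0.923 = 0.038. In this illustration best status roughly halves the contrast.

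**The case against.** A reader might infer that the article gives three incompatible definitions: week 12, any time up to week 12, and last visit. The documents do not support that. Neither any-time control nor best response is mentioned. The period clause can be read as the observation window that ends in the week-12 status named just before it, and section 2.6 supports this by giving the primary outcome week 12 only and the secondary outcomes weeks 6 and 12. Last visit is not a third definition either: it is the 12-week visit for completers, and it matches the stated LOCF rule for FAS dropouts. It also appears in a sentence about descriptive presentation, not in those on the chi-squared tests.

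It can also be said that crediting early leavers is a declared imputation rule rather than a contradiction, that the trial is exploratory, and that a condensed article may leave RECIST derivation to the full protocol.

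Most of this stands. What it does not remove is narrower. The window reading is plausible, but so is best status, and the text does not choose between them. Section 2.10.1 itself speaks of one or more measurements of the primary outcome. That LOCF is declared does not make it suitable for an endpoint in which death or later progression would be replaced by an earlier favourable scan.

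**Conclusion.** The point holds in limited form. Two classification rules are tenable for the primary endpoint, and the last-visit/LOCF rule counts patients who die or leave after an earlier SD or PR scan as controlled at 12 weeks.

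Under the stated assumptions, choosing between the two rules moves the control DCR by about 7-9 points, from 81-85% to 90-92%. LOCF moves it by about 2-3 points, to 84-87%, if dropout is independent of progression, and by more if it is not. These are illustrations built on an assumed progression curve and scan schedule, not estimates for this trial. With 22 per arm, a shift of up to two patients per arm is large enough to justify settling the rule before the data are seen.

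**What to change.** Use one rule in sections 2.6, 2.11 and 2.13:

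- Disease control is CR, PR or SD at the week-12 RECIST assessment.
- Progression or death at or before week 12 is a failure, and LOCF does not override it. Section 2.10.1 should be checked against this, because a patient who dies before any post-treatment scan does not enter the FAS as defined.
- Best status up to week 12 is reported as a secondary outcome.
- In section 2.13, the last visit is replaced by the week-12 assessment.
- The text states how patients alive without a week-12 scan are counted, and a result with all of them counted as not controlled is shown.

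The cost is wording, with no new data and no change to the 66 patients. The last item has a real downside. If the planned 30% dropout all lacked a week-12 scan, counting them as not controlled would bring the illustrative DCR to about 57-60%, some 24-26 points below the fully followed figure (0.809 - 0.566 = 0.243; 0.853 - 0.597 = 0.256), and dropout would then dominate the endpoint. It therefore belongs in a sensitivity analysis; if it is made primary, that downside should be stated.

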### Sample size calculation

2.9

The sample size was determined by considering the number of participants available, the minimum range of the efficacy assessment, and the expected dropout rate during the study period. When the first two factors were considered, the total number of participants required for each group was calculated as 15, for a total of 45. When a dropout rate of 30% was used for each group, the required number of participants was calculated as 22 (15/(1 – 0.3) = 21.43 ≒ 22). Thus, when all factors are considered, the number of participants to be registered for each group is 22, so a total of 66 patients will be recruited.

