### Analysis of second outcome variables

2.14

Descriptive statistics (number in each group, average, standard deviation, minimum value and maximum value) will be used to describe differences in the CR, PR, SD, PFS, TTP, tumor marker (CEA, NSE), WBC differential count (LMR, NLR), natural killer cell activity and QOL (EORTC QLQ-C30) between the two test groups and the control, and any differences between either of the two test groups and the control at the last visit versus baseline will be presented. The statistical significance of any difference found between test groups and the placebo group will be analyzed using chi squared test. If any difference among three groups (2 test groups and 1 placebo group) exist, Bonferroni or Duncan method will be used. Chi squared test between placebo group and treatment group 1, placebo group and treatment group 2 will be additionally conducted. The statistical significance of any variable in any group will be tested by using the paired *t* test or the Wilcoxon signed rank test.

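### CR, PR and SD are compared between arms as separate secondary outcomes; SD and PR alone have no fixed favourable direction, and no combined response rate (CR+PR) is named

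*Protocol article*

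**What the plan says.** Protocol article, section 2.6 (Outcome measures): "The secondary outcomes are comparisons of the complete response (CR) and the partial response (PR) to the treatment, the stability of the disease (SD"), followed by the remaining secondary measures, all compared among the three arms at 6 and 12 weeks. The abstract carries the same list.

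Section 2.14 (Analysis of second outcome variables) covers "differences in the CR, PR, SD, PFS, TTP, tumor marker (CEA, NSE), WBC differential count (LMR, NLR") and further items. It then assigns the tests: "The statistical significance of any difference found between test groups and the placebo group will be analyzed using chi squared test", and "Chi squared test between placebo group and treatment group 1, placebo group and treatment group 2 will be additionally conducted". It gives no favourable direction for any of the three response categories.

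The only combined response measure is the primary one. Section 2.6: "The primary outcome is a comparison of the disease control rates (DCR) among treatment groups 1 and 2 and the control group". Section 2.13 shows what DCR is built from: descriptive statistics "will be used for each variable affecting the DCR (CR, PR, and SD"). A CR+PR rate is not named in the abstract, the outcome section or the analysis sections.

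**The concern.** Under RECIST each assessed patient falls into one of CR, PR, SD or PD, so one category can grow only if another shrinks. For the two middle categories the sign of a difference does not say who did better:

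- **SD** falls if patients move up to PR or CR, and also if they move down to PD.
- **PR** falls if patients move up to CR, and also if they move down to SD.

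The primary DCR does not resolve this, because a patient who moves from SD to PR or CR counts as a success before and after. The Discussion hypothesises that HAD-B1 makes afatinib work better, and deeper response is one natural form of that. In that case DCR stays flat and SD falls. The one response summary with a clear direction, CR+PR, is not among the listed outcomes. What is at stake is how readable the secondary response results are, not the validity of the primary comparison.

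**Working it through.** **Inputs from the document.** Section 2.9: "the total number of participants required for each group was calculated as 15, for a total of 45"; 30% dropout. The enrolled figure reproduces: 15/(1 − 0.3) = 21.43, rounded up to 22 per arm, and 3 × 22 = 66. The calculations below use 15 to 22 per arm.

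**Assumptions.** The article gives no response rates, no alpha and no sidedness. All rates below are assumed, with two-sided 0.05, uncorrected chi-squared, and one dose against placebo.

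**Step 1: the identities.** DCR = CR + PR + SD, so CR+PR = DCR − SD. Each patient moved from SD to response lowers SD by one, raises CR+PR by one and leaves DCR unchanged.

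**Step 2: a worked example.** Take 22 per arm and move 6 patients from SD to PR, with z = (p1 − p2)/√[p(1 − p)(2/22)] and p the pooled rate.

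- SD 9/22 vs 3/22: p = 12/44, difference 0.273, standard error 0.134, z = 2.03, p-value 0.042. SD is significantly lower on the better arm.
- CR+PR 11/22 vs 17/22: p = 28/44, difference 0.273, standard error 0.145, z = 1.88, p-value 0.060. Response is higher.
- DCR 20/22 vs 20/22: p-value 1.00.

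If none of these patients has a CR, the PR test is the CR+PR test and gives the same 0.060.

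**Step 3: how often this happens.** Simulated trials with multinomial counts; each range runs from 15 to 22 per arm.

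| Assumed change, control to HAD-B1 | SD test | PR test | CR+PR | DCR |
|---|---|---|---|---|
| SD to PR only: PR 50→75%, SD 40→15%, PD 10% | significant fall 35–47% | significant rise 29–39% | significant rise 29–39% | significant rise 1–2% |
| Mixed: CR 5→25%, PR 45→50%, SD 40→15%, PD 10% | significant fall 35–47% | significant rise 4–5% | significant rise 29–39% | not shown; 90% in both arms |
| PR to CR only: CR 5→25%, PR 55→35%, SD 30%, PD 10% | no true change | significant fall 18–26% | no true change | no true change |
| PD to SD: PD 20→5%, SD 30→45%, PR 50% | significant rise 13–17% | no true change | no true change | significant rise 19–33% |

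A smaller SD-to-response shift (SD 30→15%, CR+PR 60→75%) gives a significant SD fall in 17–22% of trials.

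**Step 4: reading the table.** In every row HAD-B1 is better. SD falls in the first two rows and rises in the last, and PR rises in the first and falls in the third, so neither has a stable direction. The first row also shows that PR and CR+PR coincide when there are no CRs. A CR rise from 5% to 25%, as in the second and third rows, is itself significant in 31–49% of trials, so the planned CR test would register part of the benefit. CR+PR does not see the pure PR-to-CR shift in the third row; an ordered comparison of the four categories is designed to.

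**The case against.** The case for leaving the plan as it is has real force.

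- **The benefit is not hidden.** A reader might infer that a gain in objective response goes untested. With few CRs, the planned PR comparison is practically the CR+PR comparison; with many CRs, the planned CR test picks up part of the gain. What stands is narrower: no single planned comparison combines the two, and the PR test misses the gain when patients also move from PR to CR.
- **Direction can be recovered.** DCR and SD are both reported, so CR+PR = DCR − SD can be worked out by anyone. This stands for the point estimate, but it does not give the planned SD and PR p-values a direction.
- **Dose choice.** A reader might infer that the dose would be chosen on contradictory component tests. The article states no dose-selection rule and links none to CR, PR or SD, so this is not supported.
- **Number of tests.** Three categories times two doses suggests six separate tests. That is one reading; a single chi-squared test on the response table also fits the wording of section 2.14. Section 2.6 can loosely be read as pairing CR with PR. But section 2.14 lists them apart, and neither section defines a combined rate.
- **DCR treats SD and PR alike.** That is what DCR is by definition, and is no error in the secondary analysis.
- **A separate analysis plan might add CR+PR.** It might. The outcome list and its tests are nevertheless stated here, and an addition would leave the SD and PR comparisons as they are.

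**Conclusion.** The point holds in a limited form. Sections 2.6 and 2.14 set up comparisons of SD and PR whose sign cannot be interpreted alone, and they omit the directional summary CR+PR. Under the assumed mixed shift, the PR test shows the gain in about 4–5% of trials against 29–39% for CR+PR, while SD falls significantly in 35–47%. Under a pure SD-to-PR shift, PR and CR+PR perform identically, and the only harm is an SD result that could be misread as a loss; the article itself does not call a lower SD rate unfavourable.

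These figures rest on assumed response rates and an assumed two-sided 0.05 level, so they illustrate the mechanism and do not predict this trial. A reader might go on to infer that the primary analysis is compromised. It is not: the DCR test remains valid for DCR. This is a minor, cheap improvement to secondary outcomes in an exploratory trial.

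**What to change.** In sections 2.6 and 2.14, replace the separate comparisons of CR, PR and SD with one secondary response outcome, objective response rate (CR+PR), reported as the difference from placebo with a 95% CI for each dose. Present CR, PR, SD and PD by arm as a descriptive table without separate tests. If a test of the whole distribution is wanted, specify one ordered-category comparison (PD < SD < PR < CR), which also allows for movement from PR to CR that CR+PR cannot see.

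The cost is wording only, with no new data. The separate p-values for CR, PR and SD are given up. Those for SD and PR could not be interpreted alone. The one for CR does have a clear direction, so dropping it is a real if small loss, which the descriptive table and the optional ordered test partly offset.
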